### Blinding

This trial adopts a double-blind design to ensure that both participants and key study personnel remain unaware of treatment allocation. Blinding extends to participants, family members, caregivers, treating physicians, TMS operators, outcome assessors, and data analysts. Blinding procedures are outlined in the informed consent, and treatment schedules and follow-up visits are arranged to minimize potential interactions among participants.

Active and sham stimulation are delivered using a figure-of-eight double-sided coil, which has an active side for real stimulation and a placebo side that mimics the auditory and somatosensory sensations without generating an effective magnetic field. For sham stimulation, the coil is flipped, positioning the placebo side toward the scalp while maintaining an identical appearance to the active condition. To ensure full blinding, the resting motor threshold (RMT) assessment and iTBS intervention are performed by different personnel. A designated unblinded technician conducts the RMT measurement using the active side of the coil and records the motor threshold value. To preserve allocation concealment, unblinded staff label coils as “A” or “B” and perform randomization once individualized iTBS targets are determined. Only these personnel are aware of the actual mapping between labels and stimulation type. During the intervention, TMS operators are informed only which side (“A” or “B”) of the coil to use, without knowledge of the stimulation type. Imaging data are processed by blinded analysts, ensuring that group allocation remains undisclosed throughout the study.

### MRI data acquisition

All scans are conducted on a 3.0 Tesla GE SIGNA Architect scanner. High-resolution sagittal 3D T1-weighted images are acquired with a BRAVO sequence (TR/TE = 7.7/3.1 ms, FOV = 240 × 240 mm^2^, matrix = 256 × 256, slice thickness = 1.0 mm, gap = 1 mm, 176 slices). Resting-state fMRI is obtained using an EPI sequence (TR/TE = 2,500/30 ms, FOV = 240 × 240 mm^2^, matrix = 64 × 64, slice thickness = 3.5 mm, gap = 1 mm, 50 slices, 200 volumes). Participants are instructed to keep their eyes closed, stay awake, and avoid focused thinking during scanning. T2-weighted images are acquired with a turbo-spin-echo sequence (TR/TE = 5,000/120 ms, FOV = 220 × 220 mm^2^, matrix = 320 × 320, slice thickness = 5 mm, no gap, 30 slices) to identify lesion sites. Diffusion-weighted imaging (DWI) and apparent diffusion coefficient (ADC) maps are collected with TR = 3,200 ms, TE = 84 ms, and slice thickness = 5 mm. All images are visually checked for motion artifacts before analysis.

### Lesion delineation and quantification

Stroke lesions were manually delineated on T2-weighted MRI images using MRIcron (https://www.nitrc.org/projects/mricron) by two trained raters and verified by a senior neuroradiologist. Lesion masks were normalized to MNI space to calculate lesion volume and the lesion–tract overlap ratio with the left frontal aslant tract (FAT). Both indices were included as covariates in statistical analyses to control for lesion-related effects.

### pBFS mapping and white matter reconstruction

The cortical surface of a subject is subdivided, or parcellated, into functional areas based on the HCP-MMP1 (31). This atlas characterizes 180 cortical parcels on each hemisphere on the brain (360 in total) and is generated based on a large, functional neuroimaging study across a population of normal subjects in the Human Connectome Project. For each participant, the pBFS will be mapped (31) to enable correspondence between functional parcels and subject-specific white matter anatomy. Multi-direction diffusion-weighted images are preprocessed following a standardized pipeline: (1) reslicing to isotropic voxels; (2) rigid-body motion correction to the b0 reference; (3) removal of slices with excessive movement (DVARS > 2σ); (4) skull stripping using HDBET (43) with T1–DWI rigid alignment; and (5) gradient distortion correction via diffeomorphic warping between the DWI and T1 spaces (44) with T1–DWI rigid alignment. Diffusion modeling is conducted using constrained spherical deconvolution (CSD), which estimates multiple fiber orientations per voxel to resolve crossing fibers. The fiber response function is estimated per subject, and fiber orientation distribution functions (fODFs) are computed accordingly. Whole-brain deterministic tractography is performed with uniform random seeding (4 seeds per voxel; ~300,000 streamlines per brain), incorporating FA-based constraints (FA > 0.30 for seeding, termination at FA < 0.25 or curvature > 60°) to ensure anatomically plausible pathways. This reconstruction yields individualized white matter bundles connecting functional parcels across the cortex.

### Personalized stimulation target localization

Before treatment commencement, two personalized stimulation targets will be identified following the steps outlined in Figure 2. The left frontal aslant tract (FAT) is reconstructed and quantitatively assessed to determine the integrity of interconnections between the left pre-SMA and the left inferior frontal gyrus (pars opercularis).

**Figure 2 F2:**
[figure not shown]
Personalised stimulation target localisation protocol. This figure illustrates the process of localising personalised TMS targets for language rehabilitation.

The FAT's fractional anisotropy (FA) will evaluate bilaterally. The FA ratio between the affected and unaffected sides was defined as relative FA (rFA, rFA = FAipsilesional/FAcontralesional), following the method used to evaluate the corticobulbar tract (CBT) in stroke recovery (45). As defined in prior studies, an rFA > 0.5 indicates high integrity, while an rFA ≤ 0.5 indicates low integrity. It should be noted that the specific rFA threshold for defining a functionally intact FAT has not been established in the literature. Therefore, we have extrapolated from studies on other major tracts, such as the corticospinal tract (CST) and CBT, in which an rFA > 0.5 correlates with preserved motor and swallowing function (45–47). Participants with high FAT integrity receive stimulation over the ipsilesional pre-SMA, while those with disrupted FATs are stimulated over the contralesional pre-SMA.

### Treatment

All participants will receive standard medical and rehabilitation care following established clinical guidelines (43, 48, 49). Treatments will be tailored to each individual's condition and symptoms, encompassing neuroprotective interventions, risk factor management, targeted rehabilitation exercises, and specialized nursing support.

The iTBS will be delivered via a Magneuro 100 magnetic stimulation device (Vishee Medical Technology Co., Ltd., Nanjing, China), equipped with a figure-eight stimulation coil (70 mm diameter) and integrated with a neuronavigational system (Visor 2, ANT Neuro, Netherlands), using a figure-of-eight coil capable of delivering both active and sham stimulation. The rTMS was conducted to stimulate the area over the primary motor cortex (M1) of the unaffected hemisphere (50). The RMT was defined as the minimum stimulus intensity that produced a motor evoked potential (MEP) response of at least 50 μV peak-to-peak amplitude in five out of ten trials in the abductor pollicis brevis muscle of the unaffected side (51). Following this determination, participants will undergo iTBS, delivered either as active stimulation in the experimental group or as sham stimulation in the control group. The iTBS protocol comprises three sets of 600 pulses delivered daily, with each set lasting 200 s at 15-min intervals. This results in a total of 1,800 pulses per day, which are targeted at the personalized pre-SMA. iTBS will then be delivered at 80% of the individual's rMT over the pre SMA. This intensity is based on literature demonstrating the safety and efficacy of 80% rMT stimulation applied to the superior frontal gyrus in patients with post stroke aphasia, and has been shown to induce consistent excitatory effects relevant to language recovery (8). The intervention will be delivered 5 days per week over 2 weeks, totaling 10 sessions per participant. The choice of a 15-min intersession interval was based on evidence from accelerated iTBS studies demonstrating that shorter spacing between sessions maintains safety and efficacy comparable to conventional 1-h intervals while improving clinical feasibility (52–54). All TMS operators will complete standardized training and assessment prior to the trial to ensure consistency. To ensure procedural consistency, each participant will receive all treatments from a single assigned TMS operator. Following iTBS treatment, a certified speech-language therapist will administer a 30-min session of SLT for each participant.

### Outcome measures

The primary outcome of this study is the WAB, which includes four subtests: spontaneous speech, auditory verbal comprehension, repetition, and naming. Maximum attainable scores are 20 for spontaneous speech, 200 for auditory comprehension, and 100 each for repetition and naming. The AQ is then computed as: (spontaneous speech + auditory comprehension/20 + repetition/10 + naming/10) × 2. The AQ provides an index of aphasia severity and is used to evaluate changes in language function, with a maximum score of 100, a normal range of 98.4–99.6, and scores below 93.8 indicating aphasia.

Secondary outcome measures include BNT, NLCA, and resting-state fMRI. The BNT assesses confrontation naming using 30 object pictures. The NLCA evaluates nonverbal cognitive function across five domains—visuospatial ability, attention, memory, logical reasoning, and executive function—using visual materials, with a total score of 80; scores ≥75 are considered normal.

## Data analysis

### Behavioral data

Repeated-measures ANOVAs are used to assess changes in WAB, BNT, NLCA scores, and speech parameters, with phase (pre- vs. post-treatment) as a within-subject factor and group (active vs. sham iTBS) as a between-subject factor. *Post hoc* comparisons are adjusted using the Bonferroni method. Data normality is checked with the Kolmogorov–Smirnov test; non-normally distributed variables are analyzed using the Wilcoxon signed-rank test. An intention-to-treat (ITT) approach is applied in the presence of missing data.

In cases where the assumptions of normality or homogeneity of variances are violated, a non-parametric Aligned Rank Transform (ART) ANOVA was applied to test for main and interaction effects. This approach preserves the interpretability of ANOVA-type models while providing robustness to deviations from normality. For *post-hoc* comparisons, the Wilcoxon signed-rank test (within-group) and Mann–Whitney *U*-test (between-group) are used with Bonferroni correction.

To further explore variability in treatment response, a sub-analysis will be performed within the non-fluent aphasia cohort, stratifying participants according to their baseline WAB-AQ scores to examine severity-related differences in iTBS efficacy. Participants will be categorized into mild (WAB-AQ: 50.4–93.7), moderate (30.1–50.3), and severe (0–30) aphasia groups based on their baseline scores (55). Changes in primary behavioral outcomes (WAB, BNT, NLCA) will be compared across these severity strata using mixed-design ANOVAs, followed by Bonferroni-corrected *post hoc* tests. This analysis aims to explore potential differential treatment responses across varying degrees of language impairment.

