### Sample size estimation

Sample size estimation is performed using PASS software (v15.0) with reference to prior studies (42, 43). Assuming an effect size of 0.5 for WAB-AQ, a sample size of 16 per group would provide 80% power at a two-sided significance level of 0.05. To account for an anticipated 20% dropout rate, we plan to enroll 20 participants in each group.

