### Randomization

Participants will be randomly allocated in a 1:1 ratio to either the active iTBS or sham group. Randomization will be stratified by aphasia subtype (non-fluent only) to maintain balanced group allocation. The allocation sequence will be safeguarded through the use of consecutively numbered, sealed opaque envelopes, which are prepared and kept by personnel independent of the trial. Prior to the intervention, an independent researcher (not blinded) will open the corresponding envelope to determine and confirm each participant's group allocation.

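### The WAB-AQ analysis is valid but does not adjust for baseline AQ, does not show the lesion covariates stated elsewhere, and tests severity effects with no stated arm-by-severity term

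*Protocol article*

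**What the plan says.** Under Behavioral data, the article says: "Repeated-measures ANOVAs are used to assess changes in WAB, BNT, NLCA scores, and speech parameters". The model has two factors, the pre/post phase within participants and the treatment arm between them. No covariate is named. The functional connectivity and FA analyses later in the Data analysis section are likewise described with group and time only.

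Under Lesion delineation and quantification, after describing lesion volume and overlap with the left frontal aslant tract (FAT), the article says: "Both indices were included as covariates in statistical analyses to control for lesion-related effects". It does not say which analyses.

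Behavioral data also plans a sub-analysis "stratifying participants according to their baseline WAB-AQ scores to examine severity-related differences in iTBS efficacy". Participants are put into mild, moderate and severe groups by fixed AQ cut-points, and changes in WAB, BNT and NLCA are compared across those groups by mixed-design ANOVA. That description names no treatment arm. The sub-analysis is worded as exploratory.

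**The concern.** There are three linked issues.

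- **Baseline AQ.** It is one of the two response levels rather than a covariate. In a trial of 40, precision that can be had from a measurement already collected should not be given up without a reason. The change analysis also makes no correction for a chance baseline imbalance in the sample actually obtained.
- **Lesion covariates.** One section says they are in the analyses; the model descriptions do not show them. A reader cannot tell whether the main AQ result is adjusted, which leaves that choice open until the data are seen.
- **Severity.** The question is whether the active-sham difference varies with severity. Comparing changes between severity groups answers a different question, namely whether recovery differs by severity. Natural recovery and regression to the mean can both produce such a difference without any effect of iTBS.

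**Working it through.** **The plan's own figure.** The inputs under Sample size estimation are "Assuming an effect size of 0.5 for WAB-AQ" and "a sample size of 16 per group would provide 80% power at a two-sided significance level of 0.05". The dropout step reproduces: 16/(1 − 0.20) = 20 per group. The 16 does not follow if 0.5 is a standardized difference between two independent groups: n = 2(1.960 + 0.842)²/0.5² = 62.8, or 63 per group. It is reached if 0.5 is Cohen's f (a difference of 1.0 SD), or if 0.5 SD is analysed as change with r about 0.87: 62.8 × 2(1 − 0.873) = 15.9. Neither is stated. That is a separate matter; it is used here only because it bears on which r is plausible.

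**Precision.** Let r be the pre-post correlation of AQ, with equal variances SD² at both times.

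- Residual variance for change: 2(1 − r)SD².
- Residual variance for ANCOVA: (1 − r²)SD².
- Ratio, change to ANCOVA: 2/(1 + r).

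The article gives no r, so a range is assumed. Sample size per group is for a 0.5 SD difference at 80% power. Power is at 16 per group, simulated with 4,000 trials per row. The last column adds two lesion covariates that predict nothing, the worst case.

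| r | Variance ratio | n per group, change / ANCOVA | Power, change | Power, ANCOVA on baseline | Power, ANCOVA plus two useless covariates |
|---|---|---|---|---|---|
| 0.5 | 1.33 | 63 / 48 | 28% | 34% | 32% |
| 0.7 | 1.18 | 38 / 33 | 44% | 49% | 45% |
| 0.8 | 1.11 | 26 / 23 | 57% | 60% | 57% |
| 0.9 | 1.05 | 13 / 12 | 86% | 86% | 84% |

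If the lesion covariates instead explain a further 10% to 20% of residual variance (an assumption), the ANCOVA sample size falls to 43–38 per group at r = 0.5, 29–26 at 0.7 and 21–19 at 0.8.

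**How the lesion covariates enter.** Lesion volume and FAT overlap are fixed per person. Entered only as main effects in a pre/post ANOVA, they affect the between-person part of the model and leave the group-by-phase test unsharpened. They help only through a covariate-by-phase term or as covariates in a model for the post score or the change.

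**Severity strata.** Three strata by two arms make six cells: 32/6 = 5.3 people per cell among completers, 40/6 = 6.7 if all are analysed. The simulations assume baseline AQ with mean 50 and SD 22, limited to 0–93.7, the article's cut-points, and no effect modification unless stated.

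- *Smallest cell:* median 2 people. Some cell has fewer than 2 people in about 38% of trials with 32 analysed and 21% with 40.
- *Arms pooled, change compared across strata, 32 analysed:* significant in 45%, 22% and 12% of trials at r = 0.6, 0.8 and 0.9. At r = 0.5, repeated simulations gave 54% to 60%. The whole effect is regression to the mean.
- *Stratum-by-arm-by-phase term tested:* significant in about 5% of trials at every r, so type I error is held.
- *True linear modification* of 0.8 residual SD per SD of baseline AQ: power about 28% with three strata against 45% with continuous AQ (32 analysed), and 35% against 56% (40 analysed).

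**The case against.** The strongest reply is that nothing here invalidates the main test. That stands. A reader might infer that the change analysis is biased, but the article randomizes 1:1 ("Participants will be randomly allocated in a 1:1 ratio to either the active iTBS or sham group"), and the group-by-phase test is then unbiased over repeated randomizations. Baseline imbalance shifts the estimate only conditionally, in a given sample.

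The precision gain may also be small. The better baseline AQ predicts later AQ, the less change loses to ANCOVA. If the 16 per group does rest on r of about 0.87, the comparison is 16 against 15. Adding two uninformative covariates cancels the power gain by r = 0.8. That stands too, and the fix has to be judged with it in mind.

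On the lesion covariates, a reader might infer that they have been left out. The article does not support that. The lesion section can be read as supplying covariates to models described later only by their design factors, and a condensed article may leave the detail to a fuller plan. What remains is a conflict between sections that needs a clear statement.

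On severity, a reader might infer that natural recovery will necessarily be reported as an iTBS effect. That holds only if the arms are pooled. The stated aim concerns treatment response, and the other mixed-design ANOVAs in the article include group, so an arm term may be intended. The sentence does not name one, and the exploratory label does not settle which contrast is tested.

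**Conclusion.** The point holds at moderate weight. The AQ test is valid but unadjusted for baseline, at a cost of about 33% to 5% extra variance over r from 0.5 to 0.9: material at the lower end, slight at the upper. The lesion section and the model descriptions must be reconciled. The severity analysis as worded does not test its stated aim. The pooled reading gives false signals in roughly 12% to 60% of trials (r from 0.9 to 0.5). The interaction reading is sound on type I error but rests on very small cells and has less power than continuous AQ when the modification is roughly linear.

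The size depends on assumptions: r is not given, equal pre and post variances are assumed, and the strata figures rest on an assumed AQ distribution. The direction of the precision result does not depend on the value of r below 1, apart from the degrees of freedom spent.

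**What to change.** 1. Make the AQ analysis an ANCOVA of post-treatment AQ on arm and continuous baseline AQ, or the equivalent mixed model.
2. State, in the lesion section and in each of the behavioral, functional connectivity and FA analyses, which models carry lesion volume and FAT overlap, entered so that they act on the post score or the change. Settle this before unblinding.
3. Test effect modification with one exploratory arm-by-continuous-baseline-AQ term, reported with a confidence interval. Keep the three severity strata for description only.

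The cost is wording and one to three residual degrees of freedom out of 30 (32 completers less two group means). No visit or measurement changes. The downside is real: at r of about 0.8 or more, lesion covariates that are not prognostic can cancel the power gain. A single term also assumes the modification is roughly linear in AQ.

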**Methods:**

In this single-center, randomized, double-blind, sham-controlled trial, 40 participants with early subacute PSA (1–3 months post-stroke) are allocated to receive either active or sham iTBS targeting the left or right pre-SMA, localized via individualized MRI mapping. Participants will undergo a 2-week intervention, with language and neuroimaging assessments conducted at baseline, immediately post-intervention, and at a 1-month follow-up. Primary outcome measures are the Western Aphasia Battery (WAB). Second outcomes measures will be including the Boston Naming Test (BNT), the Boston Diagnostic Aphasia Examination (BDAE), non-language cognitive assessment (NLCA), alongside functional connectivity analysis from resting-state fMRI.

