## Methods

### Trial design

This investigation is designed as a prospective randomized controlled trial conducted at a single center, with a double-blind, sham-controlled structure. In total, 40 individuals with subacute PSA are enrolled from Wuxi Central Rehabilitation Hospital. The ethics approval number is WXMHCIRB2025LLky116, and the clinical registry number is ChiCTR2500108996. Participants are randomly allocated at a 1:1 ratio to either the real stimulation group or the sham stimulation group. Assessments are conducted on the enrollment day (T0) and following the completion of the iTBS intervention (T1), aphasia test batteries and fMRI are performed to evaluate language functions in PSA. Figure 1 illustrates the study design and data collection procedures, while Table 1 summarizes the timeline of enrolment and assessments.

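### The stated behavioural model has two time points, so the Day 44 language scores have no stated analysis, and the named ANOVA does not deliver the intention-to-treat statement

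*Protocol article*

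**What the plan says.** **Visits.** The Abstract describes assessments "conducted at baseline, immediately post-intervention, and at a 1-month follow-up". Table 1 ticks the WAB, BDAE, BNT and NLCA at Day 0, Day 14 and Day 44. Trial design names only two occasions: "Assessments are conducted on the enrollment day (T0) and following the completion of the iTBS intervention (T1".

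**Model.** Behavioral data names repeated-measures ANOVAs for the WAB, BNT, NLCA and some undefined speech measures. The two factors of the model are given there as follows: "with phase (pre- vs. post-treatment) as a within-subject factor and group (active vs. sham iTBS) as a between-subject factor". No other time point appears in that section.

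**Missing data.** The same section says: "An intention-to-treat (ITT) approach is applied in the presence of missing data". Sample size estimation says: "To account for an anticipated 20% dropout rate, we plan to enroll 20 participants in each group".

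**Outcome hierarchy.** Outcome measures makes the WAB primary and the BNT, NLCA and resting-state fMRI secondary. The Abstract adds the BDAE to the secondary outcomes. The severity sub-analysis in Behavioral data says: "Changes in primary behavioral outcomes (WAB, BNT, NLCA) will be compared across these severity strata".

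**The concern.** The article does not merely leave the follow-up analysis for later. It fixes a time factor with two levels, and that factor shuts out a visit which the same article schedules for every language measure. If the plan is followed as written, the trial collects one-month data and has no prespecified way to say whether any gain lasts. An analysis of Day 44 added later would be open to the charge that it was chosen after seeing the data.

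The missing-data sentence has a related weakness. Intention to treat settles who is analysed and in which arm. It does not say what happens when a score is absent, and the named model needs both scores from each participant.

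The label given to the BNT and NLCA in the sub-analysis disagrees with the outcome hierarchy set elsewhere. It is a smaller matter, but it touches the same contrast and is easily settled with it.

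**Working it through.** **1. Time points and measures, side by side**

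| Place in the Protocol article | Time points | Measures |
|---|---|---|
| Abstract, Methods | three | WAB primary; BNT, BDAE, NLCA secondary |
| Trial design | two (T0, T1) | language batteries, fMRI |
| Table 1 | Day 0, Day 14, Day 44 | WAB, BDAE, BNT, NLCA at all three; MRI at Day 0 and Day 14 only |
| Outcome measures | none given | WAB primary; BNT, NLCA secondary; BDAE not listed |
| Behavioral data | two (pre, post) | WAB, BNT, NLCA and undefined speech parameters; BDAE not named |

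A two-level time factor fits the MRI schedule in Table 1. It does not fit the language schedule.

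**2. Share of the language data without an analysis**

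Planned WAB assessments: 40 participants × 3 visits = 120. At Day 44: 40. Share: 40/120 = one third. The same share applies to the BNT and NLCA. For the BDAE, no visit enters a named model.

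**3. What the named ANOVA needs**

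With two groups and two phases, the group-by-phase test is the two-sample t-test on D = post − pre, with F = t². D does not exist for a participant without a post-treatment score, so that participant cannot contribute. The fallback methods do not change this. The signed-rank test also works on pairs, and no further time point is named for the aligned rank transform ANOVA.

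**4. How many participants could be affected**

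Inputs from Sample size estimation: 16 per group evaluable, 20% anticipated dropout.

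- The plan's own figure reproduces: 16/(1 − 0.20) = 20 per group, 40 in total.
- Anticipated dropouts: 0.20 × 40 = 8, leaving 32 (16 per group).
- The article does not say when dropout occurs. If a share s is lost before Day 14, the number without a post-treatment score is 8 × s: 8 if s = 1, 4 if s = 0.5, 0 if s = 0. Participants lost only between Day 14 and Day 44 stay in a pre/post analysis.

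**5. Bound on lost precision**

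If all 8 were missing at Day 14, the standard error with 16 per group would be √(20/16) = 1.118 times that with 20 per group. This is an upper bound on what a better model could recover, because participants with only a baseline score add little to the arm contrast. Those who miss Day 14 but attend Day 44 add more.

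**The case against.** The strongest reply is that this is a condensed article. A method for missing values is commonly left to the full protocol or SAP, and neither is shown. A two-phase ANOVA is also a valid randomised comparison at the end of treatment, and Day 44 does not affect it. The Limitation section already confines the conclusions to the short term. Covariance structure, degrees of freedom and sensitivity analyses are details for an SAP.

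Much of this stands. The end-of-treatment comparison is not invalid, and the lack of missing-data detail alone would be no finding. What remains is what the article does fix: a two-level factor that excludes a scheduled visit, and an intention-to-treat statement attached to a model that cannot carry it out.

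Three stronger readings are tempting and not supported:

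- *That the plan specifies a complete-case analysis losing up to 20% of those randomised.* The article never says complete-case. The 20% is an anticipated rate without a time point, not a cap.
- *That the arm comparison is biased by a known fraction of the planned effect.* Dropout related to severity shifts the contrast only if it differs between arms, and nothing in the article indicates that. Nor is there a scale to measure against: the plan says "Assuming an effect size of 0.5 for WAB-AQ" without stating the units.
- *That there are three co-primary outcomes with uncontrolled error.* The Abstract and Outcome measures name the WAB as primary, and the trial is sized on WAB-AQ. The conflicting label occurs once, in a sub-analysis described as exploratory.

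**Conclusion.** The point holds in limited form. The Day 44 WAB, BNT and NLCA scores have no stated analysis (one third of the planned assessments of each), and the BDAE is named in no model. The intention-to-treat sentence is not delivered by the named ANOVA. The number affected runs from 0 to 8 of 40 at the anticipated dropout, and the upper figure assumes that all of it precedes Day 14. Actual dropout could be lower or higher than anticipated. The primary label on the BNT and NLCA is a local inconsistency, not a change of hierarchy.

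This rests on the article alone. An SAP could supply a Day 44 analysis or a missing-data method, but the article's own sections would still disagree. The change should be made; the end-of-treatment comparison is not invalid without it.

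**What to change.** 1. Replace the two-phase ANOVA with a linear mixed model for WAB-AQ at Days 0, 14 and 44 in all randomised participants. Include visit and arm-by-visit terms, with baseline means constrained equal across arms. It uses every observed score and needs no complete pair. It assumes that data are missing at random given the observed scores, and this should be stated.
2. Name the arm difference in WAB-AQ at Day 14 as the single primary contrast. Make the Day 44 contrast secondary, together with the BNT, NLCA and BDAE.
3. Use intention to treat for the analysis set only, and let the model describe how missing scores are handled. A delta-adjusted sensitivity analysis for dropouts is optional.
4. Delete the word primary for the BNT and NLCA in the severity sub-analysis.
5. Reconcile the Abstract, Trial design, Table 1, Outcome measures and Behavioral data on visits and on the status of the BDAE.

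The cost is revised wording and slightly more programming. The visits are already scheduled, so no further data collection is needed.

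### A Kolmogorov–Smirnov test decides how WAB is analysed; if applied uncorrected it is a very insensitive gate at this sample size, at some cost in power but not in type I error

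*Protocol article*

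**What the plan says.** The Behavioral data section sets the default: "Repeated-measures ANOVAs are used to assess changes in WAB, BNT, NLCA scores, and speech parameters", with phase (pre, post) within subjects and group between subjects. It then states "Data normality is checked with the Kolmogorov–Smirnov test" and gives a consequence: "non-normally distributed variables are analyzed using the Wilcoxon signed-rank test". The next paragraph gives another: "In cases where the assumptions of normality or homogeneity of variances are violated, a non-parametric Aligned Rank Transform (ART) ANOVA was applied". Under this second route, post hoc comparisons use the signed-rank test within groups and the Mann–Whitney test between groups.

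The section does not state the variant of the Kolmogorov–Smirnov (KS) test, its significance level, or what is tested: raw scores, changes or residuals, per arm or pooled. Sample size estimation says "a sample size of 16 per group would provide 80% power" and plans 20 enrolled per arm to allow for 20% dropout.

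**The concern.** The classical KS test compares the data with a normal distribution whose mean and SD are fixed in advance. Here both must be estimated from the same small sample. The fitted curve then follows the data, the statistic shrinks, and the classical critical value is far too large. Lilliefors critical values correct for this; plain KS output does not.

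The test is a gate, so its sensitivity matters. If it seldom detects skew, a skewed outcome stays with the ANOVA when the plan meant it to move to a rank-based analysis. In a trial of 16–20 per arm, whose Limitation section already concedes restricted power, that could lose power on the primary outcome. Skew is plausible: WAB-AQ has a maximum of 100, entry requires a score below 93.8, and the severity sub-analysis provides for scores of 0–30.

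**Working it through.** **Inputs from the protocol.** 16 evaluable and 20 enrolled per arm; 16 / (1 − 0.20) = 20, which reproduces the enrolment figure. The trial test is two-sided at 0.05. The article states no operating characteristic for the normality check, so there is no figure of its own to reproduce on that point.

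**Assumptions.** The normality check is made at 5%. The article gives no outcome distribution, so the shapes are assumed: normal, gamma (skew 1 and 1.4), exponential (skew 2) and lognormal with sigma 1 (skew 6.2).

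**Step 1: critical values.** The statistic is D = max |F_n(x) − Φ((x − mean)/SD)|, with F_n the empirical distribution function and mean and SD taken from the sample.

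| n | classical 5% value | Lilliefors 5% value |
|---|---|---|
| 16 | 0.3273 | 0.2128 |
| 20 | 0.2941 | 0.1915 |
| 32 | 0.2342 | 0.1538 |
| 40 | 0.2101 | 0.1387 |

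At n = 20 the classical value is 0.2941 / 0.1915 = 1.54 times the appropriate one. With mean and SD known in advance, the classical test has its proper size (simulated 4.9%). With both estimated, it rejects true normality in about 0.01% of samples.

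**Step 2: detection in a single sample, n = 16 / 20 (check made per arm).**

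| Shape | KS uncorrected | Lilliefors | Shapiro–Wilk |
|---|---|---|---|
| Normal | 0.01% / 0.01% | 5% / 5% | 5% / 5% |
| Gamma, skew 1 | 0.1% / 0.2% | 15% / 19% | 23% / 29% |
| Gamma, skew 1.4 | 0.5% / 0.9% | 26% / 33% | 42% / 54% |
| Exponential, skew 2 | 2.0% / 3.9% | 48% / 58% | 71% / 84% |
| Lognormal, skew 6.2 | 12% / 20% | 68% / 79% | 86% / 93% |

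**Step 3: detection on pooled within-arm residuals of change, n = 32 to 40.** This unit of testing is more favourable to KS.

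| Shape | KS uncorrected | Shapiro–Wilk |
|---|---|---|
| Skew 1 | about 1% | 41–54% |
| Skew 1.4 | 2–5% | 69–85% |
| Exponential, skew 2 | 10–20% | 91–98% |

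Uncorrected KS detects 39–57% of lognormal samples here. For the Lilliefors version, single samples of 32 / 40 give 28% / 33% at skew 1, 49% / 59% at skew 1.4 and 81% / 90% for the exponential. That is much better than uncorrected KS and still below Shapiro–Wilk on the same samples (48% / 59%, 78% / 88% and 98% / 99.6%).

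**Step 4: type I error.** With two phases, the group-by-phase interaction is equivalent to a t-test on change. With the same skewed shape in both arms, its simulated type I error was 3.6–5.0% at 16–20 per arm. Failing to switch does not inflate it.

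**Step 5: power of the whole two-stage rule.** 20 per arm, 0.5-SD shift, pre-test on pooled residuals of change, t-test if it passes and Mann–Whitney on change if it fails.

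| Shape | gated by uncorrected KS | gated by Shapiro–Wilk | difference |
|---|---|---|---|
| Gamma, skew 1 | 34% | 39% | 5 points |
| Gamma, skew 1.4 | 36% | 45% | 9 points |
| Exponential | 46% | 60% | 14 points |
| Lognormal | 79% | 88% | 9 points |

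There is no difference for normal data. If the plan's test is the Lilliefors version, the gap to Shapiro–Wilk is about 0–2 points. The protocol writes "Assuming an effect size of 0.5 for WAB-AQ" without naming the metric. A 0.5-SD shift is one reading, so the differences matter here more than the absolute power levels.

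**Step 6: dependence on the fallback.** The gain in step 5 needs a between-arm rank test of change. With the plan's own aligned-rank ANOVA as the analysis, simulated power was only 37–43% (exponential) and 51–60% (lognormal), against 36–37% and 48–50% for the t-type test on change. A better gate in front of that fallback would recover little.

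**The case against.** The strongest reply is that the article does not say the uncorrected version is used. Output labelled Kolmogorov–Smirnov is often Lilliefors-corrected, and a condensed article can leave the variant and software to the full protocol or analysis plan. This stands: the low detection rates are conditional, and the missing variant is not itself a fault. What remains is that the article does commit to KS, and either version is less sensitive than Shapiro–Wilk.

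A reader might infer more than the documents support:

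- *That the test almost never fires.* For the uncorrected version this is fair per arm up to a skew of about 2. It is too strong for extreme skew or pooled data (39–57% for the lognormal), and wrong for the Lilliefors version.
- *That the power loss is 20 to 37 points.* Always using the t-test against always using Mann–Whitney gives 38% against 58% (exponential) and 50% against 87% (lognormal) at 20 per arm. That ignores the samples in which the gate does fire, and it is not the contrast with the plan's aligned-rank fallback. The two-stage comparison in step 5 is the relevant one.
- *That false positives increase.* They do not (step 4).
- *That the plan has no other protection.* Unequal variances also trigger the aligned-rank ANOVA, although skew of the same shape in both arms need not produce them.

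It is also fair to say that nothing in the article shows WAB-AQ change to be as skewed as an exponential or a sigma-1 lognormal.

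**Conclusion.** The point holds in conditional form and is minor. The plan lets a KS test choose the analysis of the primary outcome at 16–20 per arm. Uncorrected, that gate misses most samples with skew of 1 to 2 that Shapiro–Wilk would often or usually detect; Lilliefors-corrected, it is adequate but still the weaker choice. Against Shapiro–Wilk gating with a Mann–Whitney fallback, the cost is about 5 to 14 points of power for the skewed shapes tried if KS is uncorrected, about 0–2 points if it is corrected, and none for normal data. Type I error is not affected. The sizes rest on assumed distributions, a 5% pre-test, a 0.5-SD shift and testing of pooled residuals of change.

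The fallback matters as much as the gate. The article gives two different ones for non-normal data, and the one named first, the signed-rank test, is a paired within-group test that does not compare active with sham.

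**What to change.** Preferred: drop the normality pre-test and fix in advance one between-arm test of the change in WAB-AQ from T0 to T1. The question of variant, the insensitivity of the gate and the two competing fallbacks then disappear together.

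Alternative: replace KS by the Shapiro–Wilk test on the residuals of change (not raw scores), and name a Mann–Whitney test of change between arms as the single fallback, in place of the signed-rank test. Gate and fallback should change together, since a more sensitive gate in front of the present fallbacks brings little.

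Cost: a line or two in the analysis section, in standard software, settled before unblinding. Under the alternative, the rank-based analysis will be used more often; the simulation showed no measurable power loss from this when the data are normal.
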